### Underlying processes of errorless motor learning

1.3

The potential underlying processes of errorless motor learning have yet to be empirically tested. Owing to the implicit nature of errorless motor learning, it has been frequently suggested that it requires relatively low cognitive demands, as proposed by Maxwell et al. (2003). For example, despite cognitive impairments, children with intellectual disability who learn via errorless motor learning display improvements in gross motor skills and the ability to perform multiple tasks (Capio et al., 2013a). In other research involving adults without impairments, learning a novel locomotor task (i.e., split-belt treadmill walking) with few errors was found to be less dependent on cognitive resources—on the basis of reaction time to a secondary cognitive task—compared to when greater movement errors were generated (Sawers et al., 2013). Earlier studies demonstrated relatively greater conscious control by learners when they experienced more errors, as evidenced by increased coactivation of brain regions associated with movement processing (Zhu et al., 2011). As processing errors to adjust movement planning requires significant cognitive resources, the efficacy of errorless motor learning could be explained by the relatively reduced cognitive requirements. However, no study thus far has offered direct evidence that such cognitive factors differentiate errorless motor learning from learning with copious amounts of practice errors during the process of skill acquisition.

A behavioral representation of the cognitive processes during motor learning is the variability of movement, or trial–to–trial deviations of movement kinematics, which become evident when task difficulties vary (Lajoie and Franks, 1997). Movement variability may be considered to represent real-time cognitive engagement that is closely coupled with motor performance. Learners display relatively low movement variability when movement tasks demand high accuracy. A study of young adults engaged in a throwing task revealed greater movement variability during errorless motor learning than during errorful motor learning, and movement variability was negatively associated with conscious control (van Ginneken et al., 2018). These findings support the proposition that errorless motor learning is associated with relatively lower conscious control.

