We hypothesize that the changes during the learning phase significantly differ between errorless and errorful learning conditions for (i) movement variability, (ii) perceived competence, and (iii) PFC activity. We further hypothesize that the changes across the same variables and task performance significantly differ from before to after practice between errorless and errorful learning conditions. Finally, we will test whether the changes in task performance from before to after practice are moderated by movement variability, perceived competence, or PFC activity.

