Each experiment will be conducted over 2 days with 1 day in between, and it will consist of a pretest, a learning phase, and a posttest, as illustrated in Figure 1. The learning phase consists of two practice sessions. In each session, participants will perform 10 blocks of 15 practice trials per block, with two-minute rest periods between blocks (i.e., 150 practice trials per session). The occurrence of practice errors can be influenced by manipulation of task constraints, such as target size (Capio et al., 2013b; van Ginneken et al., 2018). As such, the practice conditions for the EL group consists of a circular target with a 100 cm radius which will be used in the first two blocks of practice; the target radius progressively decreases by 10 cm (i.e., 100 cm, 90 cm, 80 cm… 20 cm, 10 cm) after every two blocks. Thus, the target radius in the first practice session decreases from 100 cm to 60 cm, and in the second practice session, it decreases from 50 cm to 10 cm. The practice condition for the EF group consists of a circular target with a 10 cm radius which will be used throughout all practice sessions.

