### Outcome measures

2.3

The outcome measures consist of task performance, movement variability, perceived competence, and PFC activity. Covariate measures include cognitive processing speed and executive function capacity.

Task performance during the learning phase is measured by the number of successful hits on the target in each block. Task performance during the test phase is measured by accuracy scores. Task performance scores will be measured in real time by two independent observers and verified *post hoc* using video recordings of the target. The range of scores for successful hits during learning is 0–15 per block, and the ranges for accuracy during the tests are 0–100 per trial and 0–1000 for each test (Capio and Eguia, 2025).

Movement variability will be calculated using the coefficient of variation (CV) of the joint angles and joint velocity. CV is defined as the standard deviation divided by the mean (expressed as a percentage) and provides a normalized measure of how consistently joint kinematics are maintained across repeated movements (Mukherjee and Yentes, 2018). Movement kinematics will be generated using the Noraxon MyoMOTION system (Noraxon Inc., United States), which uses inertial measurement units (IMUs) to track the three-dimensional angular changes in the upper limb used for throwing. This instrument has been shown to provide valid estimates of joint kinematics (Heuvelmans et al., 2025). Four IMUs will be positioned on the (i) dorsum of the hand, (ii) dorsal side of the distal half of the forearm, (iii) lateral side of the middle third of the upper arm, and (iv) over the spine of the upper thoracic region.

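### Movement variability is defined as the CV of joint angles and velocity without limiting it to positive, true-zero quantities, so for angles it depends on coding convention and mean posture

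*Protocol article*

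**What the plan says.** Section 2.3 (Outcome measures) fixes the measure: "Movement variability will be calculated using the coefficient of variation (CV) of the joint angles and joint velocity". The formula follows: "CV is defined as the standard deviation divided by the mean (expressed as a percentage) and provides a normalized measure" of consistency across repeated movements. The signals come from a sensor system "which uses inertial measurement units (IMUs) to track the three-dimensional angular changes in the upper limb used for throwing". The article does not name the joints, axes, movement events or summary parameters, and makes no provision for means near or below zero.

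Section 1.3 describes the construct as trial-to-trial "deviations of movement kinematics, which become evident when task difficulties vary".

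The measure has several roles. Section 1.4 makes it a tested hypothesis: "We hypothesize that the changes during the learning phase significantly differ between errorless and errorful learning conditions for (i) movement variability". The same section tests its change from before to after practice. Section 2.6 models it as an outcome in its own growth model and uses the process variables as moderators of the change in performance.

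Section 2.2 sets "10 blocks of 15 practice trials per block" in each of two sessions. For the errorless (EL) arm the radius starts at 100 cm and "the target radius progressively decreases by 10 cm" after every two blocks. The errorful (EF) arm keeps a 10 cm radius throughout.

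**The concern.** Dividing an SD by a mean normalises it only if the quantity is positive and its zero means none of that quantity. A joint angle is measured from a chosen reference position, so its zero is a convention and its sign can change. SD/mean then mixes two things: how consistent the throws are, and where the average posture sits relative to that reference. Velocity has a true zero, but a component along an axis is signed and can average close to zero.

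This matters because the arms practise at different targets, and target size could alter average posture or speed. If it does, the CV moves by arm and by block with no change in consistency. The contrast at risk is time × learning condition, which tests the movement-variability hypothesis in the learning phase. The distortion could create a difference or hide a real one, and it would carry into the moderator analysis.

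**Working it through.** The article gives no figure for this point, so there is nothing to reproduce. The check applies the article's formula, CV = 100 × SD / mean. That joint angles are signed about a reference posture is general knowledge and is not stated in the article. All degree values below are assumptions.

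**1. Dependence on coding.** Take an SD of 5 degrees. An elbow held at 30 degrees of flexion is the same posture as an included angle of 180 − 30 = 150 degrees.
- Coded as flexion: 100 × 5/30 = 16.7%.
- Coded as included angle: 100 × 5/150 = 3.3%.

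The same throws with the same consistency differ fivefold.

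**2. Dependence on mean posture.** Take a constant SD of 8 degrees.

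| Mean angle (degrees) | CV = 100 × 8/mean |
|---|---|
| 40 | 20% |
| 20 | 40% |
| 5 | 160% |

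The change over time is affected too. If the SD halves in both arms, CV falls from 20% to 10% at a mean of 40 (10 points) but from 40% to 20% at a mean of 20 (20 points). Equal improvement then looks like a difference in trajectory.

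**3. Instability near zero.** Simulated blocks of 15 trials (the block size in section 2.2), SD 5 degrees, 100,000 blocks:

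| Mean (degrees) | Central 95% of sample CVs | Negative CVs |
|---|---|---|
| 90 | 3.5% to 7.6% | none |
| 5 | 54% to 210% | below 0.1% |
| 2 | −1435% to 2088% | 6% |

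**4. Whether the arms share a target when kinematics are recorded.** Section 2.3 records kinematics in blocks 3 to 8 of each session. Applying the section 2.2 schedule:

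| Blocks | EL radius, session 1 | EL radius, session 2 | EF radius |
|---|---|---|---|
| 3–4 | 90 cm | 40 cm | 10 cm |
| 5–6 | 80 cm | 30 cm | 10 cm |
| 7–8 | 70 cm | 20 cm | 10 cm |

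The arms share a target in none of the recorded practice blocks, and the EL target keeps changing while the EF target does not. At pretest and posttest both arms face the same concentric target.

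**5. Effect on a comparison of arms.** A simplified two-sample t test with 23 per arm (46/2, from section 2.1), 15 trials each, within-person SD 5 and between-person SD of mean angle 8 degrees, 4,000 replicates. True variability is equal in both arms, so every rejection is false.

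| Mean angles (degrees) | Rejections using CV | Rejections using SD |
|---|---|---|
| 60 vs 60 | 5% | 5.3% |
| 90 vs 100 | 39% | 5.5% |
| 60 vs 70 | 61% | 5.1% |
| 60 vs 80 | 99% | 5.6% |

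The bias needs a difference in mean angle but does not need means near zero. This is not the planned hierarchical model; it shows the direction and possible scale of the problem only.

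**The case against.** The strongest reply is that the article leaves the kinematic parameters unnamed, as a condensed article may, and that section 2.6 refers processing to the system's standard procedures. The reference to angular changes is compatible with excursions, which have a true zero. If only excursions and peak resultant speeds are used, with means well away from zero, the instability is small and CV is defensible. For speed, where spread can grow with the mean, a raw SD would have its own weakness. This stands, and it is why the point is limited to angles with a conventional zero and to velocity only if signed. It does not rescue the rule as written, which says joint angles without restriction.

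The degree values are all assumed, and nothing in the document shows that mean posture differs by arm or that any mean lies near zero. That stands as well.

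Section 2.6 plans diagnostics, with robust estimation or transformation if violations are found. That can limit outliers. It cannot remove dependence on coding or mean posture, and a log transform is undefined for a negative CV.

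A reader might infer three stronger things that the documents do not support:
- **That the pre-to-post comparison is exposed in the same way.** The test target is identical for both arms, so only a posture difference carried over from practice could matter there.
- **That this is the study's only behavioural marker of cognitive processing.** Section 2.2 has a dual-task transfer test, section 2.5 collects reported rules from older adults, and PFC activity is a further direct measure.
- **That section 1.3 requires the SD.** It speaks of deviations and prescribes no statistic. It describes dispersion, which the SD measures more directly, but it does not make the CV a contradiction.

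**Conclusion.** The concern holds for joint angles. As defined, the measure is not a function of consistency alone: it also reflects the angle convention and the average posture, and it breaks down near a zero mean. For velocity it holds only if signed components are used. Exposure is greatest in recorded practice blocks 3 to 8, and is limited to persisting posture differences at pretest and posttest.

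The actual size cannot be computed from the document. The illustrations rest on assumed SDs, assumed mean angles and, for the false-positive rates, assumed differences of 10 or 20 degrees between arms. With equal mean angles the CV comparison keeps its nominal 5%. This should be fixed before analysis, because the variable is a hypothesis, an outcome and a moderator. Confidence is moderate because the summary parameters are not stated.

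**What to change.** State which angular and velocity parameters enter the measure. For joint angles, define movement variability as the within-participant trial-to-trial SD per block or test, analysed on the log scale if skewed. Keep CV only for strictly positive quantities with a true zero, such as excursion or peak resultant angular speed.

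The cost is one changed derived-variable definition. The same sensor recordings serve, so the planned data collection (August 2025 to June 2026) is unaffected; the change should be documented before the kinematic data are analysed. Direct comparison with earlier reports that used CV is reduced, so CV can be given as a secondary result.

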### Safety

2.4

While two-minute rest periods between blocks are specified in the protocol across the learning and test phases, the participants will be encouraged to inform the research staff should they feel fatigue or any form of discomfort while the research staff monitor any sign of fatigue or distress. It is also acknowledged that adverse reactions may be associated with the use of Brite NIRS and IMUs. Adverse event monitoring will consist of logs maintained throughout the study, with research staff responsible for documenting any negative effects, discomfort, or unexpected responses throughout the learning and test phases. In case of discomfort or fatigue, the participants will be offered additional rest periods; they are also free to defer or withdraw their participation without any negative consequences as specified in the process of establishing informed consent. Should any unexpected findings in cortical activation or movement kinematics be observed, participants (or their guardians) will be promptly notified and referred to appropriate professionals for further evaluation as necessary. Any such adverse events or unexpected findings will be recorded, reported and followed up to ensure safety of the participants.

### Manipulation check

2.5

Task performance during the learning phase allows us to check that the EL condition indeed had significantly fewer errors during practice, indicating adherence to the intervention. A verbal protocol will also be used for older adults, with participants asked to report rules and strategies that they used when performing the throwing task (i.e., representing accumulated declarative knowledge) at the end of each practice session. Considering the emerging verbal reporting ability of children, they will be asked to demonstrate how to perform the throwing task in a step-by-step manner.

### Data processing and analysis

2.6

Data for movement kinematics and PFC activity will be processed and managed following proprietary standard procedures of the Noraxon MyoMOTION system (Noraxon Inc., United States) and Oxysoft (Artinis Medical Systems, The Netherlands), respectively. Data for task performance, perceived competence, and the covariates will be entered by research staff in real time via a customized data entry form on Qualtrics (Qualtrics LLC, United States). The identities of the participants will be known initially to the research team and recorded for purpose of matching the data from the two sessions. However, the link between participants’ identifying information and the data will only be made through codes (e.g., Participant 001). Once all data has been matched, all identifiable information will be deleted. All data files will be stored as password-protected files in the secure (i.e., password required) network drive of the first author’s affiliated university, with two-factor authentication enabled, and accessible only to the research team. A fully anonymized data file will subsequently be stored in an open science platform (https://doi.org/10.17605/OSF.IO/YTERV).

We will use random effects multilevel/hierarchical linear model (HLM) analysis to test our hypotheses. To test changes in the learning and test phases, we use the HLM approach to estimate growth curve models to examine change over time (i.e., practice blocks, test) on two levels—level one representing individual change over time and level two accounting for the extent to which change differs between age groups and between the EL and EF groups (Raudenbush and Bryk, 2002). The level one model will quantify individual changes in the measured variables (i.e., task performance, movement variability, perceived competence, PFC activity) as a function of time (i.e., practice block, test). Random slopes and intercepts will be specified for participants to account for individual differences in baseline performance and rate of change. For the level two model, fixed effects will include age group (i.e., children, older adults) and learning condition (i.e., EL, EF) as categorical predictors. Additional fixed effects will include the relevant covariates (i.e., cognitive processing speed and executive function). The random effects of the repeated measures estimate the relationship of the scores at the first time point to the rate of change over time. Planned interactions will include age group × learning condition to examine different effects of the learning condition across age groups and time × learning condition to test whether learning trajectories vary between the EL and EF conditions. Separate models will be fitted to each of the measured variables.

The statistical assumptions underlying HLM (i.e., normality of residuals, homoscedasticity, and independence of random effects) will be evaluated through diagnostic plots and residual analysis. If violations are detected, robust estimation methods or appropriate variable transformations will be applied. Missing data will be handled through maximum likelihood estimation under the assumption of missing at random (MAR) to retain all available data and minimize bias. Our data analysis approach is deemed appropriate because it allows us to track change over repeated measures and account for participants’ individual patterns of change by calculating estimates of within- and between-individual variation (O’Connell and McCoach, 2004).

To test whether the cognitive and affective process variables moderate the changes in movement performance from pretest to posttest, an HLM cross-level interaction model will be computed. We will determine whether the slope coefficients of movement performance vary across groups; a significant cross-level interaction will indicate that the slope of movement performance from pretest to posttest varies as a function of the moderators (i.e., cognitive and affective process variables) (Davison et al., 2002).

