**Figure 2 fig2:**
[figure not shown]
Diagram of the overhand throwing task in the test phase.

The pretest will be conducted on the first experimental day, immediately prior to the first practice session. It will consist of one practice trial, followed by 10 trials without any instruction or feedback (apart from being told to aim for the highest score). The posttest will be conducted on the second experimental day, immediately following the second practice session. We will adopt an A-B-A design (retention-transfer-retention) as used in motor learning studies (Maxwell et al., 2017). The first retention test will evaluate performance after the training phase; the transfer test will verify whether cognitive resources are required to support motor performance; the second retention test will assess whether any difference in performance in the transfer test was due to continued learning. The retention tests will consist of one practice trial followed by 10 trials (i.e., identical to the pretest). The transfer test consists of 10 trials with a concurrent cognitive task of counting backward (e.g., Capio et al., 2013b). The counting backward task will vary as a function of differences in cognitive ability that are associated with age. Children are asked to count backward from 100 in one (e.g., 100, 99, 98…), whereas older adults are asked to count backward from a randomly selected starting point in three (e.g., 95, 92, 89…).

Procedures for monitoring protocol adherence will include the use of attendance logs and reminders before each block to encourage engagement. We expect minimal risk of dropouts because participation will be completed within two sessions. Nevertheless, missed appointments for the second session will be followed up and rescheduled within 2 days of the original schedule. Because post-tests will be administered in the second session, participants who completely miss the said session will be excluded from data analysis. There are no requirements regarding concomitant care, but participants will be asked to report any activities that involved a similar throwing task in the day(s) intervening the two study sessions. Any deviation from the protocol, including those due to technical issues, and related concomitant care will be documented for each participant.

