Perceived competence will be measured using the corresponding IMI subscales, including adapted versions for older adults (Iwatsuki and Regis, 2021) and children (Ávila et al., 2012). The IMI uses a 7-point Likert scale (i.e., 1 = “not at all true”; 7 = “very true”). The perceived competence subscale includes statements such as “I think I am pretty good at this task,” “I was pretty skilled at this task,” and “This was a task that I could not do very well.” IMI subscales, including perceived competence, have been shown to have adequate internal consistency in the context of laboratory movement experiments (McAuley et al., 1989). While the IMI subscales have not been formally validated in our target participants, they have been used widely in motor learning studies, including those of children (Goudini et al., 2019; Levac and Lu, 2019; Drews et al., 2020) and older adults (e.g., Kappen et al., 2020; Iwatsuki and Regis, 2021; Dong et al., 2023).

PFC activity will be monitored by measurements of relative changes in oxygenated (HbO) and deoxygenated hemoglobin (HbR) levels using the Brite NIRS wireless system (Artinis Medical Systems, The Netherlands). Brite has been widely used to measure brain oxygenation in recent studies that have examined cognitive (Bhat et al., 2017) and affective (Ruotsalo et al., 2023) processes. Many studies have used the system in older adults (e.g., Goenarjo et al., 2021; Maasakkers et al., 2021; Bonnal et al., 2022) and children (e.g., Bulgarelli et al., 2023; Zheng et al., 2023; Yan et al., 2025) and have shown that it is a reliable and feasible instrument for characterizing adaptive cortical changes.

Movement kinematics and PFC activity will be measured during the pretest, across blocks three to eight in each practice session, and during the posttest. We aim to capture stable estimates of movement kinematics and PFC activity that reflect practice performance and limit the confounding effects of within-participant variability due to adaptation in the initial blocks (Eggert et al., 2021). Perceived competence will be measured after the pretest, immediately after blocks three and eight in each practice session, and after the posttest.

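### The test-phase growth curve does not test the transfer-versus-retention contrasts that the posttest was built to provide

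*Protocol article*

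**What the plan says.** **Design.** Section 2.2 (Study setting and procedures) states: "We will adopt an A-B-A design (retention-transfer-retention) as used in motor learning studies". It gives each part of the posttest a purpose. The first retention test evaluates performance after training. For the second part, "the transfer test will verify whether cognitive resources are required to support motor performance". The second retention test is there to show whether a difference at transfer reflects continued learning. With the pretest, task performance therefore has four test scores.

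**Analysis.** Section 2.6 (Data processing and analysis) will "estimate growth curve models to examine change over time (i.e., practice blocks, test) on two levels". For the random part, "Random slopes and intercepts will be specified for participants to account for individual differences in baseline performance and rate of change". The one planned interaction that involves time is "time × learning condition to test whether learning trajectories vary between the EL and EF conditions". The same specification serves every outcome: "Separate models will be fitted to each of the measured variables". The moderation analysis that closes section 2.6 asks whether one slope, from pretest to posttest, depends on the process variables.

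**Measurement schedule.** Section 2.3 (Outcome measures) states: "Perceived competence will be measured after the pretest, immediately after blocks three and eight in each practice session, and after the posttest". Movement kinematics and PFC activity are recorded during the pretest, in blocks three to eight of each practice session, and during the posttest.

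**The concern.** Retention and transfer are different conditions, one single-task and the other dual-task. They are not successive points on a learning curve. The questions in section 2.2 are differences between particular tests, whereas the model in section 2.6 yields a rate of change. A slope drawn through the transfer test blends learning with dual-task cost and isolates neither.

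This matters because section 1.2 presents the ability to perform under competing attentional demands as what chiefly sets errorless learning apart. If section 2.6 is followed as written, the test designed to show this has no matching analysis. Any later contrast would be chosen after the data are seen.

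A smaller matter is the random part. A random intercept and slope need more than two scores per participant, and perceived competence has only two in the before-to-after comparison.

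**Working it through.** **The plan's own figure.** The protocol gives no power figure for any contrast among the tests. Its sample size does not depend on this point and reproduces: f² = 0.23 with two tested predictors, alpha 0.05 and 80% power gives N = 46 per age group (power 0.81), and 46/(1 − 0.10) = 51.1, rounded up to 52.

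**1. What a linear slope sees.** Code pretest, retention 1, transfer and retention 2 as 0, 1, 2, 3. The equal spacing is an assumption. The least-squares slope has weights −0.3, −0.1, +0.1, +0.3. Applied to four condition-difference profiles:

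| Profile (pre, R1, T, R2) | True T − (R1+R2)/2 | Slope | Fitted T − (R1+R2)/2 |
|---|---|---|---|
| 0, 0, 1, 0 | +1 | 0.1 | 0 |
| 0, 1, 1, 1 | 0 | 0.3 | 0 |
| 0, 1, 0, 1 | −1 | 0.2 | 0 |
| 0, 1, 2, 1 | +1 | 0.4 | 0 |

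On a straight line the middle of three equally spaced points equals the mean of its neighbours, so the fitted transfer contrast is always zero. A difference D present only at transfer enters the slope as 0.1 D.

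**2. Illustrative power.** Assume independent within-person residuals with SD 1, D = 1, a two-sided alpha of 0.05, and a noncentral t with 2n − 2 degrees of freedom for n per arm. Then SE = √[(2/n) × Σw²].

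- Slope: Σw² = 0.09 + 0.01 + 0.01 + 0.09 = 0.20, effect 0.1.
- Transfer contrast, weights 0, −0.5, 1, −0.5: Σw² = 0.25 + 1 + 0.25 = 1.5, effect 1.

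Section 2.1 recruits 52 per age group, allocated 1:1. Section 2.6 puts both age groups in one model, so n = 52 per arm pooled, or 26 per arm within one age group. Without the attrition allowance these become 46 and 23.

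| n per arm | Slope: SE, effect/SE, power | Contrast: SE, effect/SE, power |
|---|---|---|
| 52 | 0.088, 1.14, 20% | 0.240, 4.16, 98% |
| 46 | 0.093, 1.07, 19% | 0.255, 3.92, 97% |
| 26 | 0.124, 0.81, 12% | 0.340, 2.94, 82% |
| 23 | 0.132, 0.76, 12% | 0.361, 2.77, 77% |

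**3. Random part with two occasions.** Let τ00 be the intercept variance, τ11 the slope variance, τ01 their covariance and σ² the residual variance, with times 0 and 1:

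- Var(y0) = τ00 + σ²
- Var(y1) = τ00 + 2τ01 + τ11 + σ²
- Cov(y0, y1) = τ00 + τ01

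That is three moments for four parameters (rank 3). Adding c to σ² and to τ01, while taking c from τ00 and 2c from τ11, leaves all three moments unchanged, so the data cannot choose among these splits. Three occasions give 6 moments, four give 10 and twelve blocks give 78. Each has rank 4, so the model is identified there.

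**4. What the ambiguity leaves intact.** Every such split implies the same 2 × 2 covariance matrix, so the fixed effects do not change. In one simulated two-occasion data set with 52 per arm, the random-intercept fit and the intercept-plus-slope fit both gave a time × condition estimate of 0.4926, equal to the simple difference in mean change. The SE was 0.2348 (0.2345 under one optimiser).

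**5. The alternative.** Test as a four-level factor with a random intercept has 2 variance parameters against 10 moments and is identified. A random effect for every test level plus a residual would need 10 + 1 = 11 parameters against 10 moments, so it is not identified with one score per test.

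**The case against.** **Linearity is not stated.** Section 2.6 never says that tests are scored 0 to 3 or that transfer lies on the same line. This stands as a limit, and the 0.1 D figure depends on it. But growth curve, rate of change and slope all point to a numeric score, and section 2.6 names no contrast among the tests under any coding.

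**Contrasts belong in the analysis plan, and no listed hypothesis is a transfer hypothesis.** It is true that the hypotheses in section 1.4 concern the learning phase and before-to-after change, and that contrast coding is often left to a later document. The difficulty is that section 2.6 does fix a model, and that model does not answer the questions that section 2.2 assigns to the transfer and second retention tests.

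**The identifiability problem is narrow.** This is right. A reader might infer that the specified models cannot be estimated, or will fail for every before-to-after outcome. The documents do not support that:

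- Task performance has four test scores.
- Kinematics and PFC activity are recorded during a posttest that has three parts. They are affected only if it is collapsed to one value, which the protocol does not say.
- Perceived competence has six occasions in all, and a single model over all six would be identified. The two-occasion model follows from the separate before-to-after hypothesis in section 1.4.
- Even there, only the variance split is arbitrary; the time × condition test survives. Some software may refuse the model.

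**The power figures depend on assumptions.** A reader might take 12% against 82% as this study's power. Those figures are for one age group, whereas section 2.6 pools the ages. Equal spacing, D = 1 and a difference confined to transfer are assumptions, and the pretest falls on a different day from the other tests.

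**Conclusion.** The point holds in a moderate form. Section 2.2 gives the transfer and second retention tests distinct questions, and section 2.6 plans no contrast that answers them. With numeric scoring of test, a condition difference confined to transfer reaches the slope at one tenth of its size and the transfer contrast goes untested. The illustrative power gap is about 20% against 98% with ages pooled and 12% against 82% within one age group. It rests on equal spacing, independent residuals and D of one within-person SD, none of which the protocol gives. The mismatch between the questions and the model does not depend on those values.

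The non-identified random slope is a minor matter. It is certain only for perceived competence in a two-occasion before-to-after model, and it leaves the time × condition estimate unchanged. It does affect the relation between first score and rate of change that section 2.6 says the random effects will estimate, because τ01 is part of the arbitrary split. Learning-phase models and the sample size are not affected.

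**What to change.** In the test-phase models, enter test as a categorical factor with a random intercept per participant, and plan three contrasts between the learning conditions:

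1. retention 1 minus pretest (learning);
2. transfer minus the mean of retentions 1 and 2 (dual-task cost);
3. retention 2 minus retention 1 (continued learning).

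For perceived competence before and after practice, use a random intercept only: 2 variance parameters against 3 moments. Do the same for movement variability and PFC activity if their posttest is reduced to one value. Keep random slopes for the learning-phase models, where there are enough occasions.

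The cost is a change of model wording, with no new data and no change to the sample size. Section 2 gives data collection as running from August 2025 to June 2026, so the change should be recorded before the data are analysed.
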